#### Allocation concealment mechanism and implementation

The sequence of the application of the two protocols, laser and placebo, is randomly assigned. A randomization list will be created by a random generator and kept in a locked drawer. Assignments will be kept in separate, closed opaque, sequentially numbered envelopes, enabling the sequence to be concealed until the intervention is assigned.

#### Blinding

As participants in the treatment as well as the nature of the intervention, the operator and the dental assistant will not be blinded to subjects’ group assignments. The patient will be also not blind to the treatment. The dental assistant will inform the doctor which protocol will be the first to start with and which will be the second protocol. The statistician will be blinded to treatment assignment as data will be masked before the analysis by labeling the 2 quadrants as 0 and 1, without giving the statistician the key.

#### Data collection, confidentiality, storage, and monitoring of the study documents

Collection, coding, storage, and evaluation of personal data within the project will be carried out in accordance with The General Data Protection Regulation (EU) 2016/679 (GDPR). A prerequisite for data collection will be the voluntary written informed consent of the patient’s parent or guardian. Confidentiality will be guaranteed by a coded ID number on the paper-based form, access will be granted exclusively to the study investigators. The information from the paper forms will be exported to a database file by using only the ID number and stored on a password-protected computer. Only the investigators and the statistician will have access to the final data set. All data collected on paper-based forms will be stored in sealed containers in areas of the Department of Paediatric Dentistry, Faculty of Dental Medicine, Medical University – Plovdiv, Bulgaria with limited access for 10 years in line with the Medical University of Plovdiv’s research procedures. The data custodian will be the MS.

## Statistical methods

The obtained data will be recorded, tabulated, processed, and analyzed using SPSS (Statistical Package for Social Science software) version 21.0 (IBM, USA). Descriptive statistics will be calculated. For the split-mouth randomized controlled trial Student t-test for paired samples will be used for the analysis. Mixed effects proportional odds regression modeling with outcomes of ICDAS and SOPROLIFE scores will be calculated. The inter-observer reliability and agreement will be estimated by Kappa coefficient where Kappa coefficient values above 0.80 are considered acceptable. Missing Completely at Random (MCAR) will be used to handle the missing data.

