### Eligibility

#### Inclusion criteria

Participants in the study are 12–18-year-old children, in good general health;Children, requiring fixed orthodontic treatment (fixed braces);Children at high caries risk according to “Oral disease risk assessment tool” accepted and used in the Department of Paediatric Dentistry, Faculty of Dental medicine, Medical University – Plovdiv, Bulgaria (see supplementary data file S1 “Appendix for risk assessment of oral diseases”);Children with untreated non-carious vestibular surfaces of the six maxillary anterior teeth of the permanent dentition (central and lateral incisors, canines) with ICDAS code 0 [22–24];Verbal assent from the child willing to comply with all study procedures and protocol; andObtained written informed consent by the patient’s parent/guardian for participation in the study (see supplementary data file S2 “Patient consent form” and S3 “Information leaflet”).

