#### Exclusion criteria

Children with systemic diseases that may affect oral health or oral microflora (such as diabetes);Children with medication intake that could affect the salivary flow or oral microflora (such as antibiotics);Children with mental or cognitive problems; andPatients with maxillary anterior permanent teeth affected by disturbances in the development of dental structures (hypoplasia, hypomineralization, fluorosis).

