#### Clinical protocol

First visit:
Parents/guardians are informed about the protocol of the study and the laser technique. They sign the informed consent form (see Supplementary data file S2 “Patient consent form”). Verbal assent from the child is obtained.The teeth are cleaned and polished with a rubber cup and pumice paste.A visual inspection of the vestibular surfaces of the investigated teeth and SoproLife® Daylight and SoproLife® Blue fluorescence digital images are made and recorded.Application of fluoride varnish Clinpro™ White Varnish 5% Sodium Fluoride over the whole vestibular surfaces of all anterior maxillary teethThe chosen method, CO_2_-laser irradiation or placebo, is applied.Follows direct adhesive bonding of orthodontic brackets

Second visit:
The teeth are cleaned and polished with a rubber cup and pumice paste.The incidence, extent, and severity of the lesions are assessed using ICDAS criteria and SoproLife® daylight and blue fluorescence. The data are recorded and digital photographs are made.Reapplication of the fluoride varnish Clinpro™ White Varnish 5% Sodium Fluoride

Third visit:
The teeth are cleaned and polished with a rubber cup and pumice paste.The incidence, extent, and severity of the lesions are assessed using ICDAS criteria and SoproLife® daylight and blue fluorescence. The data are recorded and digital photographs are made.Reapplication of the fluoride varnish Clinpro™ White Varnish 5% Sodium Fluoride

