#### Secondary outcome measures

The secondary outcome measures are changes in SoproLife® scores in the experimental and control teeth (within one patient) from baseline to 12 months. The SOPROlife score is a visual assessment of the caries levels. The SoproLife® daylight intraoral camera (SoproLife® Daylight mode) is used to record an intraoral picture with Sopro-imaging software (Acteon, Sopro, La Ciotat, France). The SoproLife® blue fluorescence mode scores range from 0 to 5. Code of “0” is given when the surface appears shiny green, the enamel appears sound, and there are no visible changes’ code “1” a tiny, thin red shimmer is observed, no red dots appeared; code “2” darker red spots are visible; code “3” dark red spots have extended, a slight beginning roughness of the red areas can be visible; and codes “4–6” represent larger carious lesions in dentin. Time frame: 1 year.

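### SoproLife is defined as change from baseline but the model is stated on the score; with no SoproLife entry level the two can differ, so the plan should name the baseline code as a covariate

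*Protocol article*

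**What the plan says.** Under Secondary outcome measures, the protocol article defines the outcome as "changes in SoproLife® scores in the experimental and control teeth (within one patient) from baseline to 12 months". Under Statistical methods, the regression is described in one sentence: "Mixed effects proportional odds regression modeling with outcomes of ICDAS and SOPROLIFE scores will be calculated". The sentence before it reads "For the split-mouth randomized controlled trial Student t-test for paired samples will be used for the analysis", without naming the variable to be tested.

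The Inclusion criteria require the "six maxillary anterior teeth of the permanent dentition (central and lateral incisors, canines) with ICDAS code 0". Neither the inclusion nor the exclusion criteria set a SoproLife level at entry. The exclusion criteria do remove teeth with developmental defects ("hypoplasia, hypomineralization, fluorosis").

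Baseline SoproLife is collected. At the first visit, under Clinical protocol, "SoproLife® Daylight and SoproLife® Blue fluorescence digital images are made and recorded", and Table 1 schedules both SoproLife modes before treatment, at 6 months and at 12 months.

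**The concern.** The variable named for the model is not the variable that defines the outcome. For ICDAS this has no consequence: each study tooth starts at 0, so the follow-up score and the change from baseline are the same number. For SoproLife they are the same only if every study tooth also starts at code 0, and the document does not require that. SoproLife is a separate fluorescence scale, and nothing says that ICDAS 0 guarantees SoproLife 0.

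If the follow-up code were modelled alone, the estimate would describe status at 12 months. Two things would then be at stake for this secondary outcome. Non-zero codes present equally on both sides would pull the laser estimate towards no effect. A left-right difference in baseline codes would pass into the laser estimate.

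The second risk deserves attention here because Trial design, Laser irradiation protocol and Participant's timeline all place laser on the left teeth. Sequence generation speaks of allocating quadrants, but then describes randomizing only the order of the two procedures. If the side is fixed, randomization does not balance baseline codes between laser and control teeth.

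**Working it through.** **Score against change.** Four possible SoproLife records for one tooth show where the two part:

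| Baseline to 12 months | Change | 12-month code |
|---|---|---|
| 0 to 0 | 0 | 0 |
| 1 to 1 | 0 | 1 |
| 0 to 1 | +1 | 1 |
| 2 to 1 | -1 | 1 |

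The last three differ in change but share one 12-month code. For ICDAS only records starting at 0 can occur, so the columns agree.

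**Inputs for an illustration of size.** The plan states no SoproLife figure, so there is none to reproduce.
- From Sample size calculation: lesion incidence 8.7% (control) and 3.6% (laser), and 41 patients, hence 41 x 3 = 123 teeth per side. The incidences are ICDAS figures, borrowed here for SoproLife.
- Assumed: a share b of teeth with a baseline code of 1 or more, from 0% to 20%, and no reversal of codes.
- The split at code 1 or more is one cut of the ordinal scale, chosen for arithmetic. The document sets no such threshold.

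**Equal baselines, real effect.** Proportion at code 1 or more at 12 months = b + (1 - b) x p, with p = 0.087 or 0.036. Odds ratios are laser v control.

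At b = 0 the odds ratio is (0.036/0.964) / (0.087/0.913) = 0.0373/0.0953 = 0.39 (2.55 as control v laser). At b = 5%:
- control: 0.05 + 0.95 x 0.087 = 0.1327
- laser: 0.05 + 0.95 x 0.036 = 0.0842
- odds ratio: (0.0842/0.9158) / (0.1327/0.8673) = 0.0919/0.1529 = 0.60

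| b | Teeth per side above 0 at baseline | Control | Laser | Odds ratio | Share of non-zero codes already present: control, laser |
|---|---|---|---|---|---|
| 0% | 0 | 8.7% | 3.6% | 0.39 | 0%, 0% |
| 5% | 6 | 13.3% | 8.4% | 0.60 | 38%, 59% |
| 10% | 12 | 17.8% | 13.2% | 0.70 | 56%, 76% |
| 20% | 25 | 27.0% | 22.9% | 0.80 | 74%, 87% |

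By contrast, take worsening from baseline over all teeth, (1 - b) x p, assuming teeth already above 0 do not worsen further. At b = 20% this is 0.8 x 0.036 = 0.0288 against 0.8 x 0.087 = 0.0696, an odds ratio of (0.0288/0.9712) / (0.0696/0.9304) = 0.40. It hardly moves from 0.39.

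**Unequal baselines, no effect.** Set p = (8.7% + 3.6%)/2 = 6.15% on both sides, so the true odds ratio is 1.00.
- Left 5%, right 5%: 0.05 + 0.95 x 0.0615 = 10.8% on each side. The odds ratio is 1.00, and 0.05/0.108 = 46% of the non-zero codes were there at baseline.
- Left 2%, right 4% (about 2 and 5 teeth of 123): 8.0% v 9.9%, odds ratio 0.79.
- Left 5%, right 10% (about 6 and 12 teeth): 10.8% v 15.5%, odds ratio 0.66.

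With the imbalance reversed, the last two become 1/0.79 = 1.26 and 1/0.66 = 1.51, against laser. The direction cannot be told in advance.

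**The case against.** The strongest reply is that the regression sentence lists no model terms at all. It does not name side, visit or random effects either, so silence about baseline is not exclusion of baseline. SoproLife is recorded at three time points, and a mixed model on the repeated scores with a side-by-time term would estimate change. The paired t-test could be run on change as well. Score may also be shorthand, since the primary ICDAS outcome is likewise defined as change and appears in the same sentence. This is a condensed article, and model terms are often left to the fuller plan.

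Most of this stands. A reader might infer that the trial will analyse raw 12-month codes without baseline; the document does not say so. What remains is that the one variable it does name differs from the one it defines, and that for SoproLife the two need not be equal.

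A reader might also infer that a stable tooth would be classed as diseased. That is not supported: no SoproLife disease threshold is set, and a proportional-odds model uses the ordinal code. The accurate statement is that such a tooth would sit in a higher category.

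Finally, non-zero baselines may be rare. Teeth must be non-carious and at ICDAS 0, developmental defects are excluded, surfaces are cleaned before imaging, and SoproLife code 0 is described as sound enamel. These conditions make code 0 likely but do not ensure it.

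**Conclusion.** The definition and the stated model do not match for SoproLife and should be reconciled. This is a minor point on a secondary outcome, and the primary ICDAS outcome is unaffected.

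The consequence is conditional. It arises only if the follow-up code is modelled without baseline and some teeth start above code 0. Its size is unknown, because the document gives no baseline SoproLife distribution, and it is zero if all teeth start at 0. With equal non-zero baselines the result is dilution; with unequal baselines it is bias in either direction. A fixed left side for laser makes the second case harder to dismiss.

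The odds ratios in the working are illustrations under assumed baseline shares, no reversal of codes and a borrowed ICDAS incidence. It would be tempting to read 0.79 or 0.66 as the expected error, but nothing in the document suggests that one side starts with twice the non-zero codes of the other.

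**What to change.** State under Statistical methods that each SoproLife mode is analysed by the mixed proportional-odds model on the follow-up code, with the same tooth's baseline code in the same mode as a covariate. Report worsening from baseline (12-month code above the baseline code) by side as a summary, together with the baseline distribution of codes by side. Name the variable used in the paired t-test.

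The cost is one covariate and a few words, since baseline SoproLife is already recorded on the study teeth. If every tooth starts at code 0, the covariate is constant and drops out, and nothing is lost.

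The adjustment removes only what the baseline code captures. The sections that fix laser to the left and the section that speaks of allocating quadrants must be reconciled separately.

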## Patient and public involvement

The development of the research question and outcome measures will be based on the review of available evidence in this research area. Patients will not be involved in the development of the study protocol. During the conduction of the study, patients will not be informed about the results of the ongoing trial since there is no planned interim analysis. The results will be disseminated to the study participants through email and routine follow-up dental check-ups.

## Ethics and dissemination

The clinical study will be conducted in accordance with the conditions and principles of the Declaration of Helsinki, the existing EU Clinical Trial Directive (EC) No. 2001/20/EC, the recommendations of the Ethical Committee at the Medical University of Plovdiv, Bulgaria, and the international ethical and scientific quality standard for designing, recording and reporting trials that involve the participation of human subjects - Good Clinical Practices (GCP).

### Research ethics approval

The study was approved by the Committee for Scientific Research Ethics, Medical University - Plovdiv, Bulgaria (Reference number P-605/27.03.2020, Protocol of approval No. 2/01.04.2021) and registered on a publicly accessible database ClinicalTrials.gov (Registration number: NCT03412721). Ethical approval for the study protocol and the written informed consent for all subjects’ parents/guardians was granted by the Ethics Committee of the Medical University, Plovdiv, Bulgaria.

### Consent

The operators will obtain written consent from patients’ parents/guardians willing to participate in the trial. Additional information will be provided for all parents for the study. Completed informed consent will be collected at the Department of Paediatric Dentistry, Medical University - Plovdiv by the study investigators. A copy of the signed consent form will be handed over to the participating child’s parent/guardian. After providing age-appropriate information about the study, verbal assent will be obtained as an affirmative agreement for participation from children

### Confidentiality

The information of the participants collected during the study will be kept strictly confidential and will not be disclosed to third parties. Confidentiality will be guaranteed by a coded ID number, access will be granted exclusively to the study investigators. During the planning phase of a clinical trial Medical University of Plovdiv, Bulgaria, the clinical trial sponsor, assessed that Data Monitoring Committee (DMC) was not needed for this clinical trial. As described above, a non-life-threatening procedure is the objective of this study as well as the second and third visits will be with very short duration in different timepoints for each patient. Due to this reason, the use of a DMC might not be beneficial for the study but might even delay the finalization of the trial.

### Access to data

All data collected will be stored in sealed containers in areas of the Department of Paediatric Dentistry, Faculty of Dental Medicine, Medical University – Plovdiv, Bulgaria with limited access. The information from the paper forms will be exported to a database file and stored on a password-protected computer. Only the investigators and the statistician will have access to the final data set. The quality of the clinical trial, conducted by the investigators, will be assessed by the Research Committee of Medical University of Plovdiv’s audits and regulatory inspections every 6 months.

### Dissemination policy

The results of the trial will be presented through peer-reviewed publications and conference presentations. In addition, our results will be disseminated to clinicians, as well as key stakeholders, including scientific directors of postgraduate programs “Master of Science in Lasers in Dentistry,” academic courses in Pedodontics and Preventive dentistry.

## Conclusion

This randomized control trial is a well-powered, one-center split-mouth experimental study. In split-mouth designs, experimental and control interventions are applied to different areas in the same oral cavity and the advantage is the reduction of the outcome variability estimation, leading to the potential increase in statistical power.

Fixed orthodontic treatment is associated with a high risk of initiation and development of caries lesions. CO_2_-laser has great potential in dental caries prevention. The study outlined in this protocol will be the first direct investigated combination of the preventive effect of the CO_2_-laser irradiation in addition to fluoride therapy and the fixed orthodontic treatment as a risk factor for dental caries. The implementation of CO_2_-laser in the regular protocol for the orthodontic treatment would significantly increase the success of this therapy resulting in lower rates of white spot lesions associated with it.

## Trial status

The trial is not yet recruiting patients. The process will start in September 2021 and the follow-up phase of the trial will continue until September 2023.

## Data Availability

Data available within the article or its supplementary data materials.

## Abbreviations

CO_2_: Carbon dioxide
CaF_2_: Calcium fluoride
ICDAS: International Caries Detection and Assessment System
LASER: Light Amplification By Stimulated Emission Of Radiation
SPIRIT: Standard Protocol Items for Randomized Trials
